### Statistical analysis

#### Descriptive statistics

We will report baseline socio-demographic variables for the C(E)TR and control groups (online supplemental table 1). Frequencies and percentages will be reported for categorical variables and mean (with SD) or median (with IQR) for continuous and count variables, depending on their distributions. We will describe these data separately for two diagnostic categories: (1) People with intellectual disability with/without autism and (2) Autistic people without an intellectual disability. We will compare the C(E)TR to the control group on these baseline socio-demographic characteristics using standard statistical comparisons for categorical (χ^2^) and continuous variables (t-test or Kruskal-Wallis). Descriptives of clinical variables and statistical comparisons between the C(E)TR and control groups will be provided separately for the 6 months before the index date and the 6 months after the index date. These descriptives will not lead to a causal interpretation of the effect of C(E)TRs.

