### Study eligibility criteria

Individuals of any age with a diagnosis of intellectual disability (ICD-10 code F7x) or autism (ICD-10 code F84) will be identified using diagnostic information entered into structured fields or in the free text record using the NLP diagnosis application. Participants must have a recorded diagnosis of intellectual disability and/or autism. Eligible participants must have received an episode of care from a community mental health service provided by SLaM for at least one continuous year between 1 January 2015 and 31 December 2023 to ensure that sufficient data are held in the record. All eligible episodes of care will be included, including those individuals with more than one period of community care of at least 1 year during this timeframe.

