### Matching a control group

We will match between one and five controls, who will not have a community C(E)TR, per patient who has a C(E)TR. Eligibility will be a diagnosis of intellectual disability or autism and having received a continuous period of community care within SLaM services for at least a year between 1 January 2015 and 31 December 2023. Matching will be based on age (±3 years), sex (male/female) and diagnosis (intellectual disability with/without autism, or autism without intellectual disability). Controls should be under an active episode of community care and not be an inpatient on the index date of their matched case. They must also have been under SLaM services for a similar total duration of their matched case (±2 years). Matching with replacement will be applied to ensure every case has an appropriate match according to these criteria. A pseudo-index date for each control will be assigned and will be the same as the index date of their matched case.

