### Multiple C(E)TRs

Community C(E)TRs of >6 months apart for the same patient will be treated as separate events. As community C(E)TRs require substantial planning and organisation, we expect few to take place within 6 months of a previous C(E)TR; however, if this occurs, the earlier C(E)TR date will be used as the index date and a second C(E)TR within the 6 month timeframe will be excluded from analysis.

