#### Time-to-event analysis

Time-to-discharge (length of hospital admission) will be analysed using the Kaplan-Meier estimator.^19^ A Cox’s proportional hazards model will be used to estimate the HR for discharge,^20^ comparing those who received a C(E)TR to those who did not receive a C(E)TR for a follow-up period of 6 months after admission. This analysis will be adjusted for C(E)TR status prior to admission, age at admission, sex, ethnicity and relevant diagnosis at admission (intellectual disability with/without autism, or autism alone). Patients who die within 6 months of admission will be censored at the date of death, and patients who remain in hospital will be censored at the end of the 6 months.

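### Sub-study 1 tests baseline differences as if every row were a different person, although its matching and event rules let one person supply several rows

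*Protocol article*

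**What the plan says.** All references are to the protocol article.

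- **Tests.** Under Descriptive statistics (sub-study 1), "We will compare the C(E)TR to the control group on these baseline socio-demographic characteristics using standard statistical comparisons". The methods named are χ² for categorical variables and t-test or Kruskal-Wallis for continuous ones. The section adds that, for clinical variables, "statistical comparisons between the C(E)TR and control groups will be provided separately for the 6 months before the index date", and likewise for the 6 months after. It rules out a causal reading of these results.
- **Controls.** Under Matching a control group, "We will match between one and five controls, who will not have a community C(E)TR, per patient who has a C(E)TR". Matching is on age, sex and diagnosis, with a similar time under services. Also, "Matching with replacement will be applied to ensure every case has an appropriate match according to these criteria".
- **Repeat reviews.** Under Multiple C(E)TRs, reviews more than 6 months apart "for the same patient will be treated as separate events". The Sensitivity analyses section confirms that these stay in the main analysis.
- **Status.** Profiling recipients is the first aim of sub-study 1. Table 1 lists the baseline comparison as a secondary outcome.
- **Sub-study 2.** Baseline descriptives and Pre-admission clinical and service use analysis name the same tests. Only re-admissions less than 6 months after a discharge are excluded, so a person's later admissions appear eligible.

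**The concern.** χ², t-test and Kruskal-Wallis take their null distribution from observations that are independent of one another. Here a patient with three C(E)TRs can supply three case rows, and a control drawn for four cases can supply four control rows. For a fixed trait such as ethnicity, those rows are exact copies. The tests then count more information than there is, and p-values for unmatched traits come out too small.

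At stake is the description of who does and does not receive a community C(E)TR. The Introduction hopes this profile will help target work to improve access, and a spurious difference could misdirect that work. The problem is one of variance. It arises from two written choices about the data and a written choice of test, so it is more than a detail left to an analysis plan.

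**Working it through.** **Inputs.** The article gives no sample size, significance level, control-pool size, reuse rate or number of C(E)TRs per person. Its strengths and limitations list says the number of people with a C(E)TR is unknown. There is therefore no plan figure to reproduce, and everything below is assumed: two-sided 5% level, 100 C(E)TR patients, 20 matching cells, and a person-level characteristic unrelated to the matching factors.

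**Formula.** With m rows per person, a group's design effect for a fixed trait is D = Σm² / Σm. At 1:r matching, the true variance of the group difference exceeds the assumed one by V = (D_case + D_ctrl/r) / (1 + 1/r). The actual type I error is 2 × [1 − Φ(1.96/√V)].

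**Case side.**
- 20% of patients with two C(E)TRs: D_case = (0.8×1 + 0.2×4) / (0.8 + 0.4) = 1.6/1.2 = 1.33.
- 20% with two and 10% with three: (0.7 + 0.8 + 0.9) / (0.7 + 0.4 + 0.3) = 2.4/1.4 = 1.71.
- Heavy repetition (25% two, 15% three, 10% four): (0.5 + 1.0 + 1.35 + 1.6) / (0.5 + 0.5 + 0.45 + 0.4) = 4.45/1.85 = 2.41.

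**Results at 1:5.** D_ctrl is the mean value in the simulated matching. The simulated columns use 1,500 runs each, with a t-test and an uncorrected χ² at 30% prevalence. Kruskal-Wallis was not simulated.

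| Assumed repetition | Control pool | D_case | D_ctrl | V | Formula | t-test | χ² |
|---|---|---|---|---|---|---|---|
| None | 2000 | 1.00 | 1.25 | 1.04 | 5.5% | 5.5% | 5.1% |
| 20% two | 2000 | 1.33 | 1.31 | 1.33 | 8.9% | 8.6% | 8.5% |
| 20% two | 500 | 1.33 | 2.26 | 1.49 | 10.8% | 11.5% | 11.9% |
| 20% two, 10% three | 500 | 1.71 | 2.53 | 1.85 | 15.0% | 15.1% | 14.3% |
| 20% two, 10% three | 200 | 1.71 | 4.81 | 2.23 | 18.9% | 18.6% | 19.5% |
| Heavy | 200 | 2.41 | 6.26 | 3.05 | 26.2% | 25.3% | 24.4% |
| Heavy | 100 | 2.41 | 11.53 | 3.93 | 32.3% | 35.3% | 33.6% |

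Worked line (fourth row): V = (1.714 + 2.53/5) / 1.2 = 2.220/1.2 = 1.85. Then 1.96/√1.85 = 1.44, giving 15.0%.

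**Matching ratio.** At 1:1 with 20% having two C(E)TRs and a pool of 2000, the simulated error is only 6.9% (t-test) and 6.0% (χ²).

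**Opposite direction.** If the matching cells explain 30% of a characteristic's variance, the second row falls to 3.7% / 5.7% and the fifth to 12.6% / 14.9%. Sex and diagnosis are matched exactly, so a constant ratio forces balance and the test has almost no chance to reject.

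**Remedy check.** I re-simulated the seven χ² scenarios (1,500 runs each). A person-clustered z-test rejected 5.0–6.2% of the time. A χ² test on one row per distinct person rejected 5.0–5.7%. Both are close to nominal; the Monte Carlo standard error at 5% is √(0.05×0.95/1500) = 0.6 percentage points.

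**The case against.** **The row unit is inferred.** Descriptive statistics does not say whether rows are events or people, and the matching section speaks of controls per patient. The eligibility statement "All eligible episodes of care will be included, including those individuals with more than one period of community care" concerns care episodes, not analysis rows. This is fair. However, separate events in the main analysis and reusable controls point to event rows, and no section reduces the data to one row per person.

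**The consequence is limited.** The comparisons are secondary and explicitly non-causal. The expected propensity-score variables are named in advance, with no stated selection by p-value, so nothing stated carries a false-positive baseline result into the primary estimate. This stands and bounds the severity. A descriptive p-value still has to be valid.

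**A sensitivity analysis is planned in patients with only one C(E)TR.** It belongs to the causal framework, not to these tests, and leaves control reuse untouched.

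**A fixed multiplier is tempting.** A reader might infer that true nulls are rejected two to three times too often. That needs V between 1.42 and 1.85, a middle band of assumed repetition. The scenarios run from about 1 to 7 times nominal, and the article contains nothing that selects one.

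**The models are tempting too.** A reader might infer that the length-of-stay interval, where a "proportional hazards model will be used to estimate the HR for discharge", is too narrow. The article does not establish this. Exposure is defined for each admission, as a C(E)TR in the 6 months before it, and so can change between one person's admissions. In a simulation with 200 admissions, 30% exposed, frailty SD 0.7 or 1.2 and censoring at 182 days, the naive test rejected 7.4–13.0% with exposure constant within a person. It rejected 6.8–9.2% with within-person correlation of about 0.5, and 4.3–5.7% with independent exposure. Moreover, the article names no variance estimator for the Cox, difference-in-differences, fallback logistic or HoNOS models. An article may leave that to a fuller document, so its absence is no error.

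**Conclusion.** The point holds for the named group comparisons in sub-study 1: as written, the tests do not fit the data structure. For unmatched person-level characteristics, type I error at a nominal 5% lies between about 5% and over 30% across the assumed scenarios. It is near nominal if repeat C(E)TRs and control reuse are rare, and high if repetition is heavy and the pool small. These figures rest on assumed counts and on traits fixed within a person and unrelated to the matching factors. For age, sex and diagnosis the error runs the other way, and the p-values say little because matching has already set the balance.

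The same defect extends to the sub-study 2 group comparisons wherever a person contributes more than one eligible admission; its size there was not calculated. Inflation in the difference-in-differences, Cox and HoNOS models is not established. The change should be made, but the primary analyses are not shown to be affected.

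**What to change.** - **Sub-study 1, Descriptive statistics.** State the row unit. Replace the tests with regressions of each unmatched characteristic on C(E)TR group (logistic or linear), with standard errors clustered on patient ID. A reused control keeps one ID across matched sets. Alternatively, restrict the baseline tests to one row per person.
- **Matching variables.** Describe age, sex and diagnosis by group, but do not test them.
- **Sub-study 2.** Apply the same rule to the baseline and pre-admission comparisons where a person has more than one eligible admission.
- **Precaution.** Cluster on patient ID in the difference-in-differences model, its logistic fallback, the Cox model and the HoNOS regression.
- **Reporting.** Give the number of distinct people in each group, C(E)TRs per person and uses per control, so that readers can judge how much repetition there was.

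The cost is a change of wording and a cluster option in R or Stata, with no new data. Confidence intervals become somewhat wider; if repetition proves rare, results will barely change.

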## Introduction

 Reducing unnecessary psychiatric hospital admissions and length of hospital stay for people with intellectual disability and autistic people has been a focus of English national health policy since the scandal of abuse and neglect of patients at Winterbourne View Hospital in 2011.^1^ The Transforming Care programme was established to improve community health and social care for people with intellectual disability and autistic people and to reduce what had generally been considered to be an over-reliance on inpatient psychiatric services.^2^ A key element of Transforming Care has been the introduction of Care (Education) and Treatment Reviews (C(E)TRs), person-centred review meetings that aim to ensure the right support is provided.^3^ A community C(E)TR should be convened when a person with intellectual disability or an autistic person living in the community is considered at high risk of admission to a psychiatric hospital, either because of mental ill-health or because of an escalation in behaviours that challenge. C(E)TRs are chaired by a health commissioner and include an independent clinical expert and an expert-by-experience, often a family carer of a person with intellectual disability or an autistic person. This panel gathers information from the individual, their families and carers, and professionals, and produces a report and action plan following the C(E)TR with recommendations (eg, input from specialist professionals or health teams, provision of additional care, use of respite services) that can enable the person to remain living safely in the community. Where admission to hospital is considered necessary, the C(E)TR panel will define the purpose of the admission and encourage early discharge planning in order to minimise the length of the hospital stay. Inpatient C(E)TRs are convened at various points of a hospital admission; the current project investigates only C(E)TRs that are held in the community.

Little formal research has been carried out on community C(E)TRs, such as who receives them and when, and how C(E)TRs may influence health service use, including admission to hospital. By understanding the demographic and clinical profile of patients who do, and do not, have a community C(E)TR, it may be possible to develop targeted interventions to improve access to community C(E)TRs and ensure the potential benefits are available to everyone.

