### Study aims and design

We will conduct a retrospective cohort study using a large dataset of real-world clinical data derived from Electronic Health Records (EHRs) to investigate who receives a community C(E)TR and the association of community C(E)TRs with patient outcomes and service use. This work includes two sub-studies:

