#### Sub-study 1: community cohort

We will: (1) Examine the demographic and clinical profile of those who receive a community C(E)TR and (2) attempt to model the causal relationship of receiving a community C(E)TR on the risk of psychiatric hospital admission.

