#### Sub-study 1: community cohort

Population, Intervention, Comparison and Outcome (PICO) framework (table 1).

**Table 1 T1:** Population, Intervention, Comparison and Outcome framework for sub-studies 1 and 2

	Sub-study 1	Sub-study 2
Population	People of any age with a recorded diagnosis of intellectual disability (ICD-10 code F7x), autism (ICD-10 code F84) or both, with at least 1 year of care under secondary mental healthcare services	People of any age with a recorded diagnosis of intellectual disability (ICD-10 code F7x), autism (ICD-10 code F84) or both, with at least 1 year of care under secondary mental healthcare services and an admission to a psychiatric inpatient ward for a period of at least 14 days
Intervention	Community C(E)TR	Community C(E)TR within 6 months prior to admission
Comparison	No community C(E)TR	Did not receive a community C(E)TR within 6 months prior to admission
Outcome		
Primary	Psychiatric hospital inpatient admission within 6 months of the community C(E)TR	Length of psychiatric hospital admission (days)
Secondary	Descriptive data and comparison of baseline demographics between intervention and comparison groups	Descriptive data and comparison of baseline demographics between intervention and comparison groups
	Descriptive data of 6 months pre-C(E)TR/post-C(E)TR (index date): neuropsychiatric symptoms, clinical variables and service use	Descriptive data and comparison of prehospital admission neuropsychiatric symptoms, HoNOS and service use Clinical and social functional improvement (change in HoNOS) while in hospital

C(E)TR, Care (Education) and Treatment Review; HoNOS, Health of the Nation Outcome Scales.

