### Descriptive measures

Baseline measures extracted at the index date will include age, sex, ethnicity, deprivation score (Index of Multiple Deprivation),^11^ and other socio-demographic, mental and physical health indicators (online supplemental table 1).

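### Sub-study 1 compares C(E)TR recipients only with controls matched on age, sex, diagnosis group and time under services, so it cannot show how recipients differ on those factors

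*Protocol article*

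**What the plan says.** The purpose is stated at three levels. The Introduction motivates the work with "By understanding the demographic and clinical profile of patients who do, and do not, have a community C(E)TR", so that access can be improved. Study aims and design sets out "to investigate who receives a community C(E)TR and the association of community C(E)TRs with patient outcomes and service use". The sub-study 1 aim is narrower and concerns recipients alone: "Examine the demographic and clinical profile of those who receive a community C(E)TR". Table 1 then lists as a secondary outcome of sub-study 1 "Descriptive data and comparison of baseline demographics between intervention and comparison groups", and labels the comparator simply as people without a community C(E)TR.

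The comparator actually built is the one under Matching a control group: "Matching will be based on age (±3 years), sex (male/female) and diagnosis" group. Total time under the Trust's services must also agree within 2 years. Controls take the index date of their case, one to five are used per case, and they may be reused.

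Under Descriptive measures, "Baseline measures extracted at the index date will include age, sex, ethnicity, deprivation score (Index of Multiple Deprivation" and further health indicators. Under Descriptive statistics, "We will compare the C(E)TR to the control group on these baseline socio-demographic characteristics using standard statistical comparisons", by χ², t-test or Kruskal-Wallis.

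**The concern.** Two of the variables named for the baseline comparison, age and sex, are also matching factors. So is diagnosis group, which the propensity section lists with a reference to the same supplementary table of baseline variables. Matching makes the controls resemble the cases on these factors, so the comparison reflects the sampling rule and not the population of non-recipients.

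At stake is the descriptive question, not the primary analysis. Whether recipients are younger, more often male, or more often have an intellectual disability than others on the caseload is a basic part of who receives a C(E)TR. The planned table would show near-equality on each point regardless. Table 1's plain label for the comparator makes it easier to misread that agreement as a finding.

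**Working it through.** The article gives no sample size, power or expected difference for this comparison, so there is no figure to reproduce. The check has three parts.

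**1. Algebra.** Let case *i* of *n* have a binary matched factor *x_i* (for example, male = 1) and *m_i* controls with the same value.

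- Share among cases: Σ*x_i* / *n*
- Share among controls: Σ*m_i x_i* / Σ*m_i*
- With a constant ratio *m*: *m*Σ*x_i* / (*mn*) = Σ*x_i* / *n*, so the difference is 0.

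The share among non-recipients in the population does not enter. If the ratio varies between one and five, a gap can appear, but it reflects how many controls could be found. For age, each control lies within 3 years of its case. With a constant ratio the mean difference therefore cannot exceed 3 years, and it will usually be near 0.

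Example, with assumed shares: if 35% of recipients and 20% of eligible non-recipients were under 18, the true gap is 35 − 20 = 15 points. The matched table would show about 35% against 35%.

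**2. Simulation of the matching rules.** From the article: age ±3 years, exact sex, exact diagnosis group, duration ±2 years, up to five controls, reuse across cases. Assumed: 62% male; 45% with intellectual disability; ages from a gamma distribution (shape 2.2, scale 14, limited to 5 to 85); log-linear effects on receipt of −0.03 per year of age, +0.5 for male and +0.7 for intellectual disability. A binary ethnicity variable depends on age but has no direct effect on receipt. Duration is unrelated to receipt. Each scenario had 300 runs, with on average 4.83 to 4.94 controls per case. Differences are recipients minus comparator.

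| Cases / caseload | Comparator | Age (years) | Male (points) | Intellectual disability (points) | Ethnicity (points) | Runs with p < 0.05: age, male, ID, ethnicity |
|---|---|---|---|---|---|---|
| 60 / 3,000 | All non-recipients | −8.8 | +11.2 | +17.4 | +5.4 | 97%, 44%, 79%, 15% |
| 60 / 3,000 | Matched | +0.2 | −0.4 | +0.2 | −0.9 | 0%, 0%, 0%, 6% |
| 150 / 6,000 | All non-recipients | −8.8 | +10.9 | +17.3 | +6.2 | 100%, 77%, 99%, 32% |
| 150 / 6,000 | Matched | +0.1 | −0.2 | +0.1 | −0.2 | 0%, 0%, 0%, 4% |
| 300 / 6,000 | All non-recipients | −8.8 | +11.0 | +17.4 | +6.4 | 100%, 97%, 100%, 60% |
| 300 / 6,000 | Matched | +0.1 | −0.2 | +0.1 | +0.2 | 0%, 0%, 0%, 5% |

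On the matched factors the tests reject in 0% of runs, below even the nominal 5%, because the groups have been made alike. The ethnicity column shows something different. The crude gap of 5 to 6 points comes through age, and matching removes it. The matched figure is a valid answer to a conditional question, but it is not the crude profile of recipients.

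**3. Whether another part of the plan fills the gap.**

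- Reporting by diagnostic category does not, because controls are matched within category.
- The propensity model has C(E)TR status as its outcome, but it is described only as a means of adjusting the admission analysis. Fitted to the matched set, it could not recover the effects of the matched factors.
- Sub-study 2 compares unmatched groups, but only among people admitted for at least 14 days. It does not describe the community population.

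**The case against.** The strongest reply is that the formal aim is narrower than this point supposes. The Abstract and the sub-study 1 aim speak of the profile of people who receive a C(E)TR, and describing that one group meets it in full, including age, sex and diagnosis. This stands. What is not met is the wider question in the Introduction and in Study aims and design, and the between-group comparison in Table 1.

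Second, most baseline variables are not matched. Ethnicity, deprivation, marital status, sexual orientation and psychiatric diagnoses can still differ, and a contrast conditional on age, sex and diagnosis may be the more useful one for some access questions. This also stands. A reader might infer that the whole baseline comparison is emptied by the matching. The documents do not support that; the loss is confined to the matched factors.

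Third, a reader might infer that the design hides under-provision which an unmatched table would reveal. That goes too far. The Introduction describes community C(E)TRs as intended for people at high risk of psychiatric admission, and many people on the caseload may never meet that condition. A younger recipient group could reflect greater need and not better access.

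Fourth, the matching is openly disclosed, and a careful reader would discount agreement on matched factors. That limits the risk of misreading but does not supply the missing comparison. How the descriptive tests allow for matched sets and reused controls is commonly left to a fuller plan, so it is not pressed here.

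**Conclusion.** The point holds for age, sex, diagnosis group and time under services. In sub-study 1 the comparison on these factors is near-equal by design and says nothing about who receives a community C(E)TR. Unmatched variables are compared only conditional on them. The direction follows from the matching and needs no assumption. The sizes do: the simulated gaps of about 8.8 years, 11 points and 17 points, which shrank to at most about 0.2 years, 0.4 points and 0.2 points, rest wholly on assumed inputs. Exact zero is not claimed, because the age calliper and the variable ratio can leave small residuals, which reflect the availability of controls. The simulation does not address duration, which was unrelated to receipt in it; for duration the argument rests on the ±2-year rule alone.

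Matching is a reasonable choice for the admission analysis, which this point leaves untouched. The change is worth making but does not bear on the primary outcome.

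**What to change.** For the descriptive aim, add an unmatched comparison of C(E)TR recipients with all eligible people who had no community C(E)TR. Use one record per person, and take baseline at a defined date chosen so that the calendar-time distribution is comparable between the groups. Report differences with 95% confidence intervals, or fit one multivariable logistic model for receipt. State in the plan that the table shows the recipient profile against the eligible caseload and does not measure under-provision relative to need.

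Keep the matched set for the admission analysis. Present its baseline table as a balance check with standardised differences, and name the comparator there as matched controls.

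The cost is one extra table. The Abstract says data will be extracted for all people with recorded intellectual disability and/or autism, so no new source is needed. The drawback is that the crude contrast mixes need with access, hence the required statement on interpretation.

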##### Stage 1: propensity scores

As the retrospective analysis of EHRs is not a randomised controlled study, we will employ a propensity score weighting technique to adjust for confounders in the data. Propensity scores will balance the C(E)TR and comparison groups on a set of baseline (pre-index date) characteristics.^12^ Certain characteristics may increase the probability of someone receiving a C(E)TR, and we wish to account for these in the outcome (risk of hospitalisation) model. Scores will be calculated by fitting a multivariable logistic regression model with C(E)TR status as the dependent variable.^13^ We will condition on baseline characteristics that are believed to be related to the outcome, risk of hospitalisation, and to the probability of receiving a C(E)TR (confounders), but not those that might lie on the causal pathway from receiving a C(E)TR to being admitted to hospital (mediators), that is, variables that are affected by the intervention itself. The following variables are expected to be included in the propensity score analysis: age, sex, ethnicity, marital status, sexual orientation, deprivation score, relevant diagnosis (intellectual disability with/without autism, or autism without intellectual disability) and pre-existing psychiatric diagnoses (online supplemental table 1).

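### With one to five controls per case and no matched-set weight in the descriptive comparisons, differences between groups can be created by set size alone

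*Protocol article*

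**What the plan says.** All references are to the protocol article, sub-study 1.

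- **Ratio.** Under Matching a control group: "We will match between one and five controls, who will not have a community C(E)TR, per patient who has a C(E)TR". No rule ties the number of controls to a weight.
- **Matched factors.** Age, sex and diagnostic group. Also: "They must also have been under SLaM services for a similar total duration of their matched case (±2 years"). Each control takes its case's index date, so calendar time is matched too.
- **Replacement.** "Matching with replacement will be applied to ensure every case has an appropriate match according to these criteria". This aims at a match for every case, not at the same number of controls for every case.
- **Comparisons.** Under Descriptive statistics: "We will compare the C(E)TR to the control group on these baseline socio-demographic characteristics using standard statistical comparisons for categorical" and continuous data, by chi-squared, t-test or Kruskal-Wallis. The same section adds: "Descriptives of clinical variables and statistical comparisons between the C(E)TR and control groups will be provided separately for the 6 months before the index date"; the post-index period is handled likewise. It closes with a caveat: "These descriptives will not lead to a causal interpretation of the effect of C(E)TRs".
- **Standing of these outputs.** The profile of people who receive a community C(E)TR is the first aim of sub-study 1. The baseline comparison is a secondary outcome in Table 1.
- **Primary analysis.** Stage 2 is a difference-in-differences model with propensity weights, targeting the effect in the treated. For the propensity model, Stage 1 says: "The following variables are expected to be included in the propensity score analysis: age, sex, ethnicity, marital status, sexual orientation, deprivation score", followed by diagnostic group and pre-existing psychiatric diagnoses. Time under services and index date are not named.

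**The concern.** A set with five controls supplies five times as many control rows as a set with one. Matching makes each set comparable. It makes the pooled groups comparable only if every set carries the same weight on the control side. An ordinary two-group test on pooled rows does not give that.

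The number of controls found for a case plausibly depends on how common that combination of age, sex, diagnosis and time under services is in the register. If so, people with common combinations are over-represented among the controls, and the groups can differ on the matched factors themselves, or on anything related to them. A reader of the profile table could then take a by-product of set size for a feature of who receives a C(E)TR. The introduction wants these profiles to guide better access, so the description matters in its own right.

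**Working it through.** The protocol gives no figure to reproduce: set sizes are not stated, and it says the number of people with a community C(E)TR is unknown. The inputs below are therefore assumptions, apart from the one-to-five range.

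**1. Formula.** Let t be the share of cases of a hard-to-match type, with k controls each, and let the remaining cases have 5 controls each. The pooled, unweighted share of that type among controls is

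tk / (tk + 5(1 − t)).

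Matching within sets is taken as perfect, so the correct share is t.

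**2. 100 cases, k = 2.**

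- t = 0.30: 30 × 2 = 60 and 70 × 5 = 350 controls. Share 60/410 = 14.6% against 30% of cases; Pearson chi-squared p = 0.0003.
- t = 0.10: 10 × 2 = 20 and 90 × 5 = 450 controls. Share 20/470 = 4.3% against 10% of cases; p = 0.02.

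The p-values treat control rows as independent, which matching with replacement may break, so they are only a guide. The shares do not depend on this.

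**3. Range.** With half the cases easy to match at 5 controls each:

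| Controls per hard-to-match case | Easy type among controls (cases: 50%) | Standardised difference |
|---|---|---|
| 5 | 50.0% | 0 |
| 4 | 55.6% | 0.11 |
| 3 | 62.5% | 0.25 |
| 2 | 71.4% | 0.45 |
| 1 | 83.3% | 0.76 |

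**4. Spill-over to other variables.** The false difference in a feature is (t − control share) × (its prevalence gap between the two types). At t = 0.30 and k = 2 the first term is 0.30 − 0.146 = 0.154. A feature present in 80% of one type and 20% of the other would differ by 0.154 × 0.6 = 0.092, about 9 points. At 50% and 30% it would differ by 0.154 × 0.2 = 0.031, about 3 points.

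**5. Effect of a set weight of 1/(controls in the set).** For t = 0.30: 60 × 1/2 = 30 and 350 × 1/5 = 70, so the share is 30/100 = 30%, equal to the cases.

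**6. Primary analysis.** Assume the usual weights for the effect in the treated, e/(1 − e), where e is the propensity score.

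- With the matched factor in the model, e is 1/3 in the hard-to-match stratum (30 cases, 60 controls) and 1/6 in the other (70 cases, 350 controls). The weights are 1/2 and 1/5, and the weighted share is 30/(30 + 70) = 30%. The unequal ratio is undone.
- With the factor left out, the weights do not depend on it, so the share stays at 14.6%, apart from any correlation with variables that are in the model.
- Multiplying set weights into propensity weights from an unweighted fit over-corrects: 60 × 1/2 × 1/2 = 15 and 350 × 1/5 × 1/5 = 14, giving 15/29 = 51.7% against 30%. For t = 0.10: 5/(5 + 18) = 21.7% against 10%.

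**The case against.** **The article never says the comparisons are unweighted, and such detail often sits in an analysis plan.** This is partly right. But the article does name the tests, and ordinary two-group tests do not fit the variable ratio it also names. Ordinary unweighted tests are the plain reading.

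**The imbalance is not certain.** This stands. It vanishes if all cases reach the same number of controls, or if that number is unrelated to their characteristics, and replacement makes full sets easier to reach. A reader might infer that the control group will differ from the cases; the protocol supports only that it can.

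**The comparisons are declared non-causal, and data are described separately by diagnostic group.** Both are true. The first limits the harm but does not make an artefact of set size a sound description. The second largely removes the problem for diagnosis in the description, but not for age, sex, time under services or index date.

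**The primary estimate is protected.** This mostly stands. A reader might infer that the main effect estimate inherits the pooling problem. The protocol does not support that for age, sex and diagnosis, which are in the propensity model. For time under services and index date, differencing removes stable level differences, so bias needs trends that vary with those factors. The list is also only of variables expected to be included, and the supplement it points to is not shown. The exposure lies mainly in the fallback, a logistic regression on post-index status alone, which has no such differencing.

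**Conclusion.** The point holds in a limited, conditional form. The one-to-five ratio and the named tests do not fit together unless controls are weighted by set. The consequence falls mainly on the descriptive baseline and before/after comparisons, which serve a stated aim and a secondary outcome.

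Its size cannot be found from the document. Under the assumed set sizes, the standardised difference on a matched factor runs from 0 (equal sets) to 0.76 (half the cases with five controls, half with one).

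For the primary analysis the residual issue is narrower: two matched factors, time under services and index date, are not named for the propensity model. No bias in the primary estimate has been shown. It would matter chiefly if the logistic fallback were used.

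**What to change.** 1. Under Descriptive statistics, weight each control by 1/(number of controls in its matched set) in every table and comparison with the C(E)TR group, using weighted versions of the tests. Alternatively, fix the matching ratio.
2. Under Stage 1, add index year and time under services to the propensity model.
3. Report the distribution of set sizes, and weighted balance on all matching factors: age, sex, diagnosis, index date and time under services.
4. Do not multiply set weights into propensity weights from an unweighted fit, because those weights already undo unequal set sizes for modelled factors. If set weights enter the outcome model, fit the propensity model with them too.

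The cost is one weight column and two covariates, settled before results are seen, and slightly wider intervals. In the 30% illustration the effective number of controls is (sum of weights)²/(sum of squared weights) = 100²/(60 × 0.25 + 350 × 0.04) = 10,000/29, about 345 instead of 410. A fixed ratio avoids the weights, but it discards controls from larger sets or depends on every case reaching that number.
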